### Ethics and Quality Standards

The study was presented to the local ethics committees in Nigeria and Indonesia to receive ethics agreements for health research using humans as research subjects. In Nigeria, the study was granted approval by the State Universal Basic Education Board before enrollment of the schools. In Indonesia, the study was granted approval by the Health Research Ethics Commission at the Faculty of Dental Teaching, Trisakti University, also before the enrollment of the schools. The study was registered with ClinicalTrials.gov (NCT04001296).

It is the responsibility of the LSC to ensure that the study is conducted in accordance with the principles of Good Clinical Practice, 2008 version of the Declaration of Helsinki, and applicable local laws and regulations concerning studies conducted on human subjects that are outside of the definition of a medicinal product or medical device. Quality assurance audits may be performed by the sponsor or any ethics committee or regulatory authority during the course of the study or at study completion.

### Study End Points

#### Assessment of Behavioral Change Impact

The objective of this study is to evaluate the impact of educational school programs in improving the oral health of local communities. The primary objective of the study analysis will be to measure the impact on knowledge, behavior, and toothbrushing habits in school children in Indonesia and Nigeria after a 21-day school program. This will be evaluated using three questions (specifically questions on behavior and knowledge) from the children’s questionnaire at all evaluation points (T0, T0+21, T1, T2). Improvement in knowledge and behavior will be calculated based on the percentage of positive change. Positive change is considered when a child selects the correct answers of twice daily brushing with a fluoride toothpaste.

The secondary objective employs the use of the OHI-S to assess plaque levels. More frequent brushing will result in lower plaque levels compared with baseline and compared with control groups. Plaque levels will be used to validate reported brushing frequency with assessments timed to align with questionnaire completion (how well are the children retaining and acting on the information/motivation delivered by the 21-day intervention?). To evaluate the longer term impact of the 21-day program on knowledge/behavior and oral health in children after periods of 8 weeks and 24 weeks, the children in the test group should report higher levels of brushing frequency and reduced plaque levels compared with children in the control group. To provide evidence that the 21-day school program is effective in getting parents and carers to also improve their brushing habits and to brush day and night, parents’ own brushing frequency, use of fluoride toothpaste, amount of toothpaste, and toothbrushes purchased should increase when compared with baseline and compared with parents in the control group. To measure the change in quality of life, well-being, and social measures of school children after a 21-day oral health program, children may report less dental discomfort/pain and need to take fewer days off school as a result. Additionally, at baseline (T0) and T2, all children will be scored for their caries prevalence using the DMFT index. No direct conclusions on the caries can be made but it is important descriptive information that is often not available in these two countries and could serve further research.

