### Selection of Schools

This is a cluster randomization trial with schools being the clusters, randomized to intervention or control groups. Schools need to be matched in terms of setting (city, suburb, rural) and socioeconomic status. The sample size calculation determined the number of schools that would be required to detect a difference between the test and control groups. The response of interest is an improvement in brushing behavior.

For Nigeria, it is assumed that 30% of the children are already brushing twice a day [6]. The trial is designed to detect a minimum 35% difference in the number of children brushing day and night at day 22 between the intervention group and the control group. It is assumed that the control group will see a 20% increase in proportion of children brushing twice a day due to the free toothpaste and toothbrushes they are given (Hawthorne effect). The interclass correlation has been set low at 0.05 and 0.10 (ie, low interpupil correlation) as we do not expect the children to influence each other in their brushing behavior because brushing will be carried out at home.

For Indonesia, it is assumed that 84% of the children are already brushing twice a day [6]. The trial is designed to detect a minimum 30% difference in the number of children brushing day and night at day 22 between the intervention and control group. It is assumed that the control group will have 40% of children brushing twice per day as a result of the Hawthorne effect. Again, the interclass correlation has been set at 0.05.

Therefore, for both Nigeria and Indonesia, the target number of schools is 20 (10 intervention and 10 control schools) calculated using power 80% and a significance level of .05. This number of clusters should also be sufficient to detect a difference of 0.5 in the OHI-S (plaque) at the same power and significance level. About 30 children in each class, in each grade, are anticipated, and for each child, the participation of a parent completing the questionnaires at each time point will be requested.

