#### Questionnaires

This study aims to understand, to a greater extent, the impact of the 21-day BDN program on quality of life–related outcomes and, thus, includes more detailed questions and addresses some aspects of the new oral health definition [11].

The parent questionnaire includes 14 main questions addressing aspects on oral health behavior and knowledge, socioeconomic factors, well-being, and quality of life–related outcomes. Most of the parent questions were taken from validated questionnaires, namely the World Health Organization oral health surveys, Global Oral Health Assessment Index, and Positive Oral Health and Well-being 15-term [12-14]. Other questions were developed through a process in which an expert group identified topics included in similar surveys and developed questions on these topic areas adapted to the study objectives and setting. Parent questions can be found in Multimedia Appendix 4.

The children’s questions were derived from the parent questions and adapted for children’s comprehension and to obtain the required information as set by the objectives of the study. In addition, building on learning gained in the previous study [6], the questionnaire was further refined to remove overlapping answers encountered that required some retrospective reinterpretation prior to analysis.

The children’s questionnaire includes 8 main questions to address the primary objective of improvement in behavior and knowledge, adapted to their comprehension.

Did you brush your teeth yesterday?If yes, how many times?Did you brush your teeth today?If yes, how many times?How often do you brush your teeth at home?Most days, do you brush your teeth both in the morning and the evening?Do you think it is important to brush your teeth every day?If yes, how often should you brush your teeth every day?

An intense immersion into a fun and engaging 21-day BDN program will inform children of the importance of twice a day brushing with a fluoridated toothpaste and motivate improved brushing frequency. This will be seen in results of questionnaires issued to children at time points throughout the study. All children’s questions can be found in Multimedia Appendix 5.

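### The sample size is set on twice-daily brushing alone, but the scoring rule adds fluoride toothpaste, the listed questions omit it and Table 2 separates the two, so the 80% power is not tied to one primary outcome

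*Protocol article*

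**What the plan says.** Four places in the protocol article describe the primary outcome.

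- **Selection of Schools** (sample size): "The response of interest is an improvement in brushing behavior". The Nigerian baseline is given as follows: "it is assumed that 30% of the children are already brushing twice a day". The Nigerian target reads: "The trial is designed to detect a minimum 35% difference in the number of children brushing day and night at day 22". For Indonesia the trial is to "detect a minimum 30% difference in the number of children brushing day and night at day 22", with 40% assumed in controls. Fluoride is not part of the event. The result is 10 schools per arm in each country at 80% power and a .05 significance level.
- **Assessment of Behavioral Change Impact** (scoring): the primary objective is evaluated from three questions, which are not named, and improvement is the percentage of positive change. "Positive change is considered when a child selects the correct answers of twice daily brushing with a fluoride toothpaste".
- **Questionnaires**: the child instrument "includes 8 main questions to address the primary objective of improvement in behavior and knowledge". The eight cover brushing yesterday and today, how many times, usual frequency at home, morning and evening brushing, whether daily brushing matters, and how often one should brush. None mentions toothpaste or fluoride. The full instrument is in Multimedia Appendix 5, which is not shown.
- **Table 2**, primary row: three child-questionnaire variables are listed side by side, namely reported brushing frequency, knowledge that twice a day is needed, and reported fluoride toothpaste use.

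**The concern.** The event that was sized, the rule for scoring a child as improved, the questions said to feed that rule and the variables in the analysis table should describe the same thing. Here they do not. The sized event is brushing frequency. The scoring rule adds a fluoride condition. The printed question list cannot supply that condition. The table splits the outcome into three.

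Two things are at stake. First, the headline result could be computed in more than one way from the same data: brushing alone, brushing together with fluoride, or three separate results. Second, the stated power belongs to only one of these. Both arms receive fluoride toothpaste, so a fluoride condition might separate the arms little while lowering the rate in each. In that case the contrast on the joint event would be smaller than the one the trial was sized for.

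**Working it through.** **Inputs, from Selection of Schools.** 10 schools per arm. ICC 0.05 and 0.10 (Nigeria) and 0.05 (Indonesia). About 30 children per class and grade. The cluster size used in the calculation is not given, so m = 30 and m = 90 (three grades, one class each) are both shown. The percentages are read as absolute:

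- Nigeria: control 30 + 20 = 50%, intervention 50 + 35 = 85%.
- Indonesia: control 40%, intervention 40 + 30 = 70%.

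A two-sided test is assumed.

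**The plan's own figure.** Two-proportion sample size with pooled variance, times the design effect 1 + (m − 1)·ICC, divided by m:

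- Nigeria: 27 children per arm before clustering. For m = 30 and 90 this is 2.2 and 1.6 schools per arm at ICC 0.05, and 3.5 and 3.0 at ICC 0.10.
- Indonesia: 42 children per arm, or 3.4 and 2.5 schools at ICC 0.05.

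The stated 10 per arm is not reproduced. It is more than these inputs need, and power for brushing alone exceeds 99% in both countries. Reading the percentages as relative gives 10.1 schools for Nigeria (50% vs 67.5%, m = 30, ICC 0.05), but 22.1 for Indonesia (40% vs 52%, m = 30). No single reading returns 10 in both countries. What follows uses the absolute reading, which leaves the most room.

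**Joint event, equal fluoride share.** Assumption: a share q of twice-daily brushers also gives the fluoride answer, the same in both arms. The documents give no value for q. The rates become 0.50q vs 0.85q (Nigeria) and 0.40q vs 0.70q (Indonesia). The variance per arm is p(1 − p)[1 + (m − 1)·ICC]/(10m), and power is from a noncentral t on 18 df.

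Worked case, Nigeria, q = 0.5, m = 30, ICC 0.10:

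- Rates 0.25 vs 0.425, difference 0.175, design effect 3.9.
- Variance of the difference = (0.1875 + 0.2444) × 3.9/300 = 0.00561, so SE = 0.0749.
- Ratio 0.175/0.0749 = 2.34, power 60%.

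| q | Nigeria (ICC 0.10, m = 30, to ICC 0.05, m = 90) | Indonesia (ICC 0.05, m = 30 to 90) |
|---|---|---|
| 0.8 | 93% to >99% | 96% to 99% |
| 0.5 | 60% to 90% | 71% to 83% |
| 0.3 | 34% to 62% | 44% to 56% |

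The share at which power reaches 80%, for m = 30 and m = 90:

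- Nigeria, ICC 0.05: 0.50 and 0.41.
- Nigeria, ICC 0.10: 0.66 and 0.60.
- Indonesia, ICC 0.05: 0.58 and 0.47.

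**Joint event, share raised by the programme.** Same formula, different q by arm:

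- 0.5 control, 0.6 intervention: Nigeria 25% vs 51%, power 90% to >99%. Indonesia 20% vs 42%, power 95% to 99%.
- 0.3 control, 0.5 intervention: power at least 96% in both countries.
- 0.5 control, 0.8 intervention: Nigeria 25% vs 68%, a difference of 43 points, larger than the 35 that was sized.

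**The case against.** A reader might infer that the primary outcome counts only the joint event. Table 2 does not support that. It lists brushing frequency as a primary variable in its own right, and Statistical Analysis says that each measure in the table is compared. The scoring sentence speaks of three questions and of answers in the plural, which could mean three items each scored separately. This stands: the joint reading is the most natural one, but not the only one.

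A reader might also infer that no fluoride item exists. Table 2 takes fluoride use from the child questionnaire, the Abstract names it as a child measure, and the full questionnaire is in an appendix that is not shown. This stands too: the printed list of primary questions lacks the item, but that does not show the instrument lacks it.

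The third tempting inference is that the trial is underpowered. Adding a condition cannot raise a rate, but it can widen a difference. The programme teaches brushing with fluoride toothpaste and controls do not receive it, so a higher share in the intervention arm is plausible, and a modest rise is enough to keep power high. The low-power figures need a share that is both low and equal in the two arms, and the documents give no value.

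None of this removes the inconsistency. Table 2 adds a further description of the outcome, and nothing in the protocol says which one the 80% power serves.

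**Conclusion.** The point holds as an inconsistency in how the primary outcome is defined. The power statement covers reported twice-daily brushing and is not established for the score in Assessment of Behavioral Change Impact.

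The effect on power is conditional. With an equal share in both arms and absolute differences, joint-event power drops below 80% at shares under roughly 0.4 to 0.65. With a rise from 0.5 to 0.6 in the intervention arm it is at least 90%. These figures rest on an assumed share, assumed cluster sizes of 30 or 90 and no dropout. They show what the answer depends on and do not demonstrate a shortfall.

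The Indonesian inputs are taken as printed here. The protocol states that "it is assumed that 84% of the children are already brushing twice a day" and yet assumes 40% in controls. That is a separate matter.

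**What to change.** In Assessment of Behavioral Change Impact, define the primary score as the child's report of brushing twice a day at T0+21, which is the event sized in Selection of Schools. Name the question that supplies it, because several of the eight could: the number of times yesterday, the usual frequency at home, or brushing both morning and evening. Report knowledge and fluoride use as separate items, as Table 2 lists them, and name the fluoride question in the Questionnaires section. Make the count of primary questions (three or eight) agree.

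If the joint event is kept as primary, restate the power for it under a stated fluoride share in each arm, and show how power changes with that share.

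The cost is wording in these sections and in the analysis plan, with no new data. The choice should be recorded before results by arm are examined. The downside is that fluoride use, a stated target of the programme, no longer counts in the headline score.

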#### Questionnaires

This study aims to understand, to a greater extent, the impact of the 21-day BDN program on quality of life–related outcomes and, thus, includes more detailed questions and addresses some aspects of the new oral health definition [11].

The parent questionnaire includes 14 main questions addressing aspects on oral health behavior and knowledge, socioeconomic factors, well-being, and quality of life–related outcomes. Most of the parent questions were taken from validated questionnaires, namely the World Health Organization oral health surveys, Global Oral Health Assessment Index, and Positive Oral Health and Well-being 15-term [12-14]. Other questions were developed through a process in which an expert group identified topics included in similar surveys and developed questions on these topic areas adapted to the study objectives and setting. Parent questions can be found in Multimedia Appendix 4.

The children’s questions were derived from the parent questions and adapted for children’s comprehension and to obtain the required information as set by the objectives of the study. In addition, building on learning gained in the previous study [6], the questionnaire was further refined to remove overlapping answers encountered that required some retrospective reinterpretation prior to analysis.

The children’s questionnaire includes 8 main questions to address the primary objective of improvement in behavior and knowledge, adapted to their comprehension.

Did you brush your teeth yesterday?If yes, how many times?Did you brush your teeth today?If yes, how many times?How often do you brush your teeth at home?Most days, do you brush your teeth both in the morning and the evening?Do you think it is important to brush your teeth every day?If yes, how often should you brush your teeth every day?

An intense immersion into a fun and engaging 21-day BDN program will inform children of the importance of twice a day brushing with a fluoridated toothpaste and motivate improved brushing frequency. This will be seen in results of questionnaires issued to children at time points throughout the study. All children’s questions can be found in Multimedia Appendix 5.

#### Simplified Oral Hygiene Index

The OHI-S [15] is a rapid method for evaluating oral cleanliness of population groups. In this study, the following permanent teeth will be scored: 16, 11, 26, 46, 31, and 36. However, due to the specific target age group of the study, the equivalent deciduous teeth 55, 51, 65, 85, 71, and 75 will be scored when the above-mentioned permanent teeth are not present.

#### Decayed, Missing, and Filled Teeth Index: Tooth Level

The DMFT index [14] has been used for more than 70 years and is well established as the key measure of caries experience in dental epidemiology. The DMFT index can be applied to both the permanent and primary dentition. Table 1 shows the full schedule of study end points by time point and intervention for this study. The schedule is the same for control and intervention groups.

**Table 1 table1:** Study end points by time point and intervention.

Group and end point		Baseline T0	T0+21^a^	T1^b^	T2^c^
**Children**					
	Questionnaire	x	x	x	x
	OHI-S^d^	x	x	x	x
	DMFT^e^	x			x
**Parents/carers**					
	Questionnaire	x	x	x	x

^a^T0+21: end of 21-day intervention.

^b^T1: 8 weeks after the end of the intervention.

^c^T2: 24 weeks after the end of the intervention.

^d^OHI-S: Simplified Oral Hygiene Index.

^e^DMFT: Decayed, Missing, and Filled Teeth index.

### Data Management

#### Data Exclusion

All school data will be used, and where a school has been significantly noncompliant (eg, a school has not sufficiently followed and completed all elements of the 21-day BDN program) with the protocol, this will be registered. Minor deviations may be included at the discretion of the LSC. Participants who missed more than 5 days (one school week) of the 21-day BDN program will have this information registered in the analysis.

#### Data Handling and Record Keeping

Paper forms (Multimedia Appendix 6) will be used to collect all questionnaire answers from parents and children as well for reporting the oral health indicators used, the OHI-S and DMFT. All collected data will be compiled using SPSS Statistics (IBM Corp) software for study analysis.

The LSC will keep a separate confidential enrollment log that matches identifying codes with children’s names and addresses. The LSC will maintain these documents at the site. It is the responsibility of the LSC or designee to maintain adequate clinical study records. Copies of all clinical study material must be archived for a period of at least 15 years after the end of the study (or more as legally required). All documents must be archived in a secure place and treated as confidential material. The anonymous data will be made available to researchers upon request.

### Statistical Analysis

As outlined in Table 2, five outcomes measures have been prepared and prioritized to evaluate the effect of the 21-day program. At each time point, summary statistics will be calculated for intervention and control schools and include within- and between-group analyses.

Each of the mentioned measures in Table 2 will be compared between T0 and T0+21 and between T0 and T0+21 and T1 and T2 for the intervention and control groups. The mean change will be reported, with 95% confidence interval and associated *P* value. Longitudinal models will be used. Multinomial logistic regression will be performed when the outcome variables have a nominal level of measurement. For ordinal and interval outcome variables, we will use either ordered logistic or linear regression as appropriate. To measure positive change, we will convert nominal or ordinal independent variables using dummy variables where each dummy will be measuring the effect of one answer category on the reference category.

Each of the above measures will be compared between the intervention and control group at T0, T0+21, T1, and T2 using analyses of covariance, mixed models, and generalized estimating equations as appropriate. Mean differences will be reported, with 95% confidence interval and associated *P* value.

In addition to analyzing the impact of the program on various beneficiaries through behavior and health change, the global impact of the 21-day program will be analyzed. This analysis will be performed by multivariate analysis, which measures the influence of each outcome variable on the others and of each independent variable on the relevant outcome variables. We will also measure some of the variables with a measurement model such as factor analysis. All statistical analyses will be performed using SPSS Statistics software.

To minimize bias in the results, the intention to treat principle will be applied and every randomized participant will be analyzed. The school structure is helping us to minimize missing data, but it may still occur due to the longitudinal aspect of the study and number of follow-ups. In this case, carrying the last data forward should be the best approach.

**Table 2 table2:** Study objectives as they relate to the statistical analysis plan.

Objective	Outcome variables	Results observed for	Hypotheses
Primary: measure the impact on knowledge/behavior and toothbrushing habits in school children after a 21-day school program and compare with baseline and a control group	Child questionnaire: reported brushing frequency, knowledge of the need to brush twice a day, reported use of fluoride toothpaste	within-group analysis: T0+21 vs T0; between-group analysis: T0, T0+21	Immersion in a structured 21-day school program will inform children of the importance of twice a day brushing with a fluoridated toothpaste and motivate improved brushing frequency.
Secondary: measure the impact on oral health via plaque levels in school children after a 21-day school program and compare with baseline and a control group	Child clinical observation: plaque levels (OHI-S^a^) will be used to validate reported brushing frequency with assessments timed to align with questionnaire completion (how well are the children retaining and acting on the information/motivation delivered by the 21-day intervention?)	within-group analysis: T0+21 vs T0; between-group analysis: T0, T0+21	More frequent brushing will result in lower plaque levels compared with baseline and compared with their control group.
Tertiary: evaluate the longer term impact of the 21-day program on knowledge/behavior and oral health in children after a period of 8 weeks (T1) and 24 weeks (T2) or approximately 7 months total	Child questionnaire: reported brushing frequency at T1 and T2; knowledge of the need to brush twice a day and reported use of fluoride toothpaste at T1 and T2; and OHI-S at T1 and T2 compared with baseline, after 21 days, and with control group	within-group analysis: T2 vs T0, T0+21, and T1 vs T0, T0+21; between-group analysis: T0, T0+21, T1, T2	Children in the intervention group will report higher levels of brushing frequency and reduced plaque levels compared with the children in the control group. This can be attributed to the 21-day intervention.
Quaternary: provide evidence that the 21-day school program is effective in getting parents and carers to also improve their brushing habits and to brush day and night.	Parent questionnaire: reported brushing frequency, reported use of fluoride, renewing toothbrush frequency, amount of purchased toothpaste	within-group analysis: T0+21 vs T0; between-group analysis: T0, T0+21	Consenting for their children to participate in a toothbrushing program will likely trigger a reflection upon their own oral care habits, and parents’ own brushing frequency, use of fluoride toothpaste, amount of toothpaste, and toothbrushes purchased should increase when compared with baseline and compared with parents in the control group.
Quinary: measure the change in quality of life, well-being, and social measures of school children after a 21-day oral health program	Child questionnaire: reported absenteeism for oral health issues	within-group analysis: T0+21 vs T0; between-group analysis: T0, T0+21	Children may report less dental discomfort/pain and a need to take fewer days off school as a result.

^a^OHI-S: Simplified Oral Hygiene Index.

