### Study Design

This study is a 2-arm, superiority cluster randomized trial. Clusters in this study are infant and junior schools in Indonesia and Nigeria. Schools will be matched into pairs by location and then randomized to intervention and control groups using a randomization table.

The study will look to recruit children aged 6 to 9 years in school grades 1, 2, and 3 to participate in the study. Children who assent to take part in the study (see Multimedia Appendix 2 for form), meet the selection criteria, and have the informed consent of their parents (see Multimedia Appendix 3 for form) will be enrolled in the study. The study flowchart is shown in Figure 1.

The T0 (baseline), T0+21 (end of 21-day intervention), T1 (8 weeks after the end of the intervention), and T2 (24 weeks after the end of the intervention) data collection time points will consist of questionnaire completion and a clinical assessment of plaque level evaluation using the Simplified Oral Hygiene Index (OHI-S) and an additional caries evaluation at T0 and T2 using the Decayed, Missing, and Filled Teeth index (DMFT). For the control group, the same flowchart will be followed, but the “Start 21-day BDN program/Finish 21-day BDN program” is replaced by only providing toothpaste and toothbrushes to school children.

The delivery of the intervention program relies on Unilever materials including toothpaste and toothbrushes as well as all the necessary educational materials. These materials are produced and delivered by Unilever locally. Translations of the materials to a local language will be completed if necessary. Toothpaste provided in Indonesia will be a commercially available and marketed product manufactured by Unilever Indonesia containing 1450 ppm fluoride as 1.12% sodium monofluorophosphate in a chalk base (Pepsodent Anti-Cavity or similar). In Nigeria, a commercially available and marketed toothpaste sold by Unilever Nigeria containing 1450 ppm fluoride (0.32% sodium fluoride) in a silica abrasive (Pepsodent Cavity Fighter Gel or similar) will be provided.

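### Within-arm P values against baseline stand beside the between-arm tests for every objective, and nothing says that only the between-arm contrast decides whether the program works

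*Protocol article*

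**What the plan says.** Study Design states: "This study is a 2-arm, superiority cluster randomized trial".

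Statistical Analysis plans two sets of comparisons for all Table 2 measures.

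- **Over time, within each arm.** "Each of the mentioned measures in Table 2 will be compared between T0 and T0+21", and then against the later visits, for intervention and control groups. On the output: "The mean change will be reported, with 95% confidence interval and associated" P value.
- **Between arms.** "Each of the above measures will be compared between the intervention and control group at T0, T0+21, T1, and T2", by analysis of covariance, mixed models or generalized estimating equations, with mean difference, interval and P value.

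In Table 2 the primary, secondary, quaternary and quinary rows each read "within-group analysis: T0+21 vs T0; between-group analysis: T0, T0+21". The tertiary row reads "within-group analysis: T2 vs T0, T0+21, and T1 vs T0, T0+21; between-group analysis: T0, T0+21, T1, T2". The secondary hypothesis is "More frequent brushing will result in lower plaque levels compared with baseline and compared with their control group", and the quaternary (parent) hypothesis has the same two-part form. The primary and secondary objectives are themselves worded as comparisons with baseline and with control.

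Selection of Schools says of Nigeria: "It is assumed that the control group will see a 20% increase in proportion of children brushing twice a day". It attributes this to the free toothpaste and toothbrushes (Hawthorne effect).

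**The concern.** Randomization isolates the program only through the difference between arms. The intervention arm's change from baseline mixes three things: the program, the free supplies that both arms get, and the effect of being questioned and examined, which follows the same schedule in both arms (Table 1). For Nigerian brushing the protocol expects the last two to move the outcome on their own. There, by its own assumption, the null hypothesis of the pre-post test is false even if the program is inert.

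As written, the two kinds of P value have equal standing as ways to evaluate the program's effect. A report could present a significant gain from baseline as support for an objective while the between-arm difference is inconclusive, and the protocol contains no sentence that would prevent it.

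**Working it through.** **Plan's own figure.** The protocol gives no figure for the within-arm tests. Its one related figure, 10 schools per arm, does not follow from its inputs at face value: Nigeria at 50% vs 85% needs 2 to 5 schools per arm. This point takes only the number of schools from it.

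**What each test addresses.** Let s be the change from supplies and observation, and τ the program's effect. The intervention arm's expected change is s + τ and the control arm's is s. The within-arm test has null s + τ = 0; the between-arm test has null (s + τ) − s = τ = 0. If τ = 0 and s > 0, the first null is false and the second is true.

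**Inputs from Selection of Schools.** Nigerian baseline p0 = 0.30. The control rise of 20% is read as percentage points (p1 = 0.50) or as relative (p1 = 0.30 × 1.20 = 0.36), since the protocol does not say which. There are 10 schools per arm, intraclass correlation 0.05 and 0.10, and significance level .05 (two-sided assumed). About 30 children per class in three grades gives m = 30 to 90 per school, so n = 300 to 900.

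**Assumed, not in the document.** Within-child correlation 0 to 0.5; correlation of a school's level between visits 0 or 0.8; no program effect.

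**Calculation A: paired proportions.** With d = p1 − p0 and D = p0(1 − p1) + p1(1 − p0) − 2φ√[p0(1 − p0)p1(1 − p1)]:

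SE = √[(D − d²) × DE / n], where DE = 1 (no clustering) or 1 + (m − 1) × 0.05, and φ = 0 or 0.4.

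- 30% to 50%, φ = 0, m = 30: D − d² = 0.50 − 0.04 = 0.46 and DE = 2.45. SE = √(0.46 × 2.45/300) = 0.0613, z = 0.20/0.0613 = 3.26, power 0.90 (normal) or 0.83 (t, 9 df). This is the lowest case; the highest exceeds 0.99.
- 30% to 36%, φ = 0, m = 30: D − d² = 0.444 − 0.0036 = 0.4404. SE = √(0.4404 × 2.45/300) = 0.0600, z = 1.00, power 0.17 (normal) or about 0.14 (t).
- 30% to 36%, φ = 0.4, m = 90, clustered: D − d² = 0.2644 and DE = 5.45. SE = 0.0400, z = 1.50, power 0.32 (normal) or 0.27 (t).
- The same without clustering: SE = √(0.2644/900) = 0.0171, z = 3.50, power 0.94 (normal).

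**Calculation B: school and child components.** With within-child correlation ρ and school autocorrelation c:

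Var = [p0(1 − p0) + p1(1 − p1)]/(10m) × [(1 − ICC)(1 − ρ) + m × ICC × (1 − c)].

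- 30% to 50%, ICC 0.10, m = 30, ρ = c = 0: SE = √(0.46 × 3.9/300) = 0.0773, z = 2.59, power 0.73 (normal) or 0.64 (t). Once ρ is 0.3 or 0.5 and c is 0.8, as suits the same children and schools measured twice, power is at least 0.98.
- 30% to 36%, the same low case: SE = √(0.4404 × 3.9/300) = 0.0757, z = 0.79, power 0.12 (normal) or 0.11 (t). High case (ICC 0.05, m = 90, ρ = 0.5, c = 0.8): SE = √(0.4404 × 1.375/900) = 0.0259, z = 2.31, power 0.64 (normal) or 0.54 (t).

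| Reading of 20% | A | B | Overall |
|---|---|---|---|
| 30% to 50% | 0.83 to >0.99 | 0.64 to >0.99 | 0.64 to >0.99 |
| 30% to 36% | 0.14 to 0.94 (clustered only: 0.14 to 0.32) | 0.11 to 0.64 | 0.11 to 0.94 |

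**Indonesia.** The printed figures are 84% at baseline and 40% in controls. Taken literally, the pre-post test would be significant almost always (probability about 1.0), but for a fall.

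**The case against.** The strongest reply is that the right analysis is already there. Every measure is compared between arms with a difference, interval and P value; the sample size is built on a between-arm difference at day 22; and the Discussion rests the evaluation on the control schools. Within-arm results printed alongside bias no estimate and do not inflate the error of the between-arm test. The plaque and parent hypotheses require a gain over baseline and over control, so a baseline gain alone does not satisfy them. The tertiary hypothesis rests on control alone. An analysis plan that is not shown may name the confirmatory contrast.

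Much of this stands, and it rules out stronger readings that a reader might infer:

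- **That the trial repeats the earlier study without controls.** It does not: there is a control arm, and a between-arm test for every objective.
- **That significant gains are to be expected for all objectives whatever the program does.** The 20% is stated for Nigeria and twice-daily brushing only. No control-arm change is assumed for plaque, parents or absenteeism, and Indonesia's figures point downward.
- **That a significant Nigerian gain is the expected result on any reading.** That needs the percentage-point reading. On the relative reading, significance is often the less likely outcome, and the 94% arises only with no clustering, 900 children, φ = 0.4 and a normal reference.
- **That one arm's P value will be set against the other's in place of a direct test.** The protocol does not plan this.

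The reply does not remove the core. The protocol itself attaches P values to the within-arm changes and words objectives as comparisons with baseline, without ranking the two contrasts. That is stated text, not detail left for later.

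**Conclusion.** The point holds in limited form. Within-arm P values are planned for every objective, they cannot isolate the program, and the protocol does not say that the between-arm contrast alone decides.

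The size is shown for Nigerian twice-daily brushing, under no program effect and the assumed correlations above: roughly 64% to over 99% significant on the percentage-point reading and 11% to 94% on the relative one. Applying a clustering of 0.05 directly to change narrows the relative range to about 14% to 32%. Every value is above the 5% of a valid test, so the conclusion does not depend on which reading is meant; only its size does.

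For the other outcomes the argument is structural: a change within one arm cannot separate the program from what both arms share. The planned between-arm estimates are not affected. The risk lies in what may be claimed from the other set of P values.

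**What to change.** 1. In Statistical Analysis and Table 2, report within-arm changes descriptively, as estimate and confidence interval without a P value.
2. State there that each objective is judged on the cluster-adjusted between-arm difference at its time point.
3. Remove improvement over baseline as a criterion from the objectives and from the plaque and parent hypotheses, in Table 2 and where Study Objectives and Study End Points repeat it.
4. Separately, reconcile Indonesia's 84% baseline with its 40% control figure, and say whether Nigeria's 20% is in percentage points or relative.

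Items 1 to 3 change wording only. No data, sample size or between-arm power is lost; the sponsor gives up a set of P values that say nothing about the program.
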